#### Factors that may affect MBC implementation

The iPARIHS framework guides our assessment of factors that may affect implementation. Table 2 shows data sources that will provide information for the assessment of the iPARIHS dimensions. Some of these data sources also address measures for the RE-AIM evaluation of the implementation facilitation (IF) strategy and were previously described.

##### Facilitation

Assessment of facilitation includes both self-reported documentation of activities by the external facilitators and SMEs, and, data collected from QI team members on IF activities. Because comparison sites will not receive facilitation, assessment of *Facilitation* will only be conducted at intervention sites.

**Documentation of the facilitation strategy**Facilitation activities will be documented using two data collection mechanisms. First, we will conduct bi-weekly to monthly debriefing interviews with the external facilitators and SMEs and use summary notes to document on-going facilitation, QI team processes, and factors that might foster or hinder MBC implementation at each intervention site. Second, facilitation team members will document their time, activities, and numbers and roles of site personnel on activity logs in preparation for a time-motion analysis of facilitation activities. Debriefing interview and time-motion data will enable us to go beyond determining whether the EF + QI team strategy is effective and to offer possible explanations for why it is or is not effective within particular organizational contexts and how facilitators can enhance MBC implementation.

**QI team interviews**To assess the facilitation process from the perspective of QI team members, semi-structured qualitative group interviews will be conducted with QI team members at intervention sites at two time points (see Fig. 2). The first interview will assess QI team accomplishments and functioning, the value of the facilitation process, and how it might be improved. The second interview will focus on MBC implementation and factors that affected it, results of and concerns about using MBC, MBC sustainment, and experiences with facilitation.

##### Context

We will assess select organizational factors at all 12 study sites with two validated instruments to enhance our understanding of contextual factors that may have affected MBC implementation.

**Provider survey: Organizational Readiness for Change (ORC)**To assess baseline organizational functioning and climate at intervention and comparison sites, we will administer the ORC, which is considered to have good validity [55]. Similar to other VA implementation studies [56, 57], we will minimize participant burden by administering only ten of the ORC subscales across three domains, including: motivation to change subscales (program needs, training needs, and pressures for change), an adequacy of resources subscale (staffing), and, organizational climate subscales (mission, cohesion, autonomy, communication, stress, and, change) [58].

**Provider survey: Primary Care Behavioral Health Provider Adherence Questionnaire-2 (PPAQ-2)**The PPAQ-2 is a scale of behavioral health provider protocol adherence to PCMHI. This adherence is thought to be essential to BHPs’ ability to function as part of the primary care team. The original PPAQ has been shown to have strong psychometric properties [59]. The recently revised and expanded version, PPAQ-2, has shown excellent reliability and validity through confirmatory factor analysis [60]. The study will use the following content domains: Practice and Session Management; Referral Management and Care Continuity; Consultation, Collaboration, and Interprofessional Communication; Patient Education, Self-Management Support, and Psychological Intervention; and Panel Management. Higher PPAQ-2 scores indicate high fidelity to PCMHI.

**Other data sources**In addition to the ORC and PPAQ-2, data sources addressing RE-AIM measures will also inform our understanding of the context for MBC implementation. For example, the team communication interviews and TDM will provide us with additional information about the organizational culture and the MBC qualitative interviews will provide us with information about the contextual barriers to and enablers of change for MBC implementation. At the intervention sites, the debriefing interviews will be particularly rich sources of information about the organizational context across organizational levels.

##### Innovation and recipients

Some of our data sources will provide us with information about the characteristics of the innovation, e.g., MBC interviews and MBC use surveys (underlying knowledge sources, clarity and usability). They will also provide us with information about the recipients, e.g., Team communication interviews and TDM (collaboration and teamwork); QI team interviews (motivation to change and beliefs) and MBC interviews (values). Again, the debriefing interview data will provide us with a rich description of the recipients and the innovation at intervention sites.

### Aim 2 data collection

To study the association between team communication and functioning and MBC implementation, individual semi-structured qualitative interviews will be conducted with primary care (providers and nurses) and PCMHI providers at the facilitation intervention sites. These interviews will be conducted at two time points (see Fig. 1). Interview items reflect constructs related to team functioning in health care settings [61]. These items are tailored specifically for the topic of caring for primary care patients with mental health conditions: communication across primary care and PCMHI providers; impact of MBC implementation on provider communication; cohesiveness among team members; perceptions of professional role clarity; and perceptions of common team goals. Additionally, during the second interview, providers’ attitudes about the acceptability, feasibility and utility of using MBC will be assessed.

### Data analysis

The data analysis plan is designed to allow for triangulation across data sources in order to inform the two study aims. General analytic approaches are described first, followed by the planned strategies for addressing the two study aims.

#### Aim 1 data analysis

Administrative data will be used to compare rates of PROM administration and entry into the EMR across intervention and comparison sites. The analytic strategy will be to compare rates between the intervention and comparison sites at the end of the intervention and after a sustainment period while controlling for the baseline rate of use. Chart review data will be analyzed by calculating descriptive statistics for patient background/demographics, PCMHI service utilization, patient diagnoses, and, PCMHI provider type. Descriptive statistics will also be used to characterize PCMHI provider documentation of MBC elements including administration of measures of interest (i.e., PHQ-9, PCL, BAM, GAD-7, others) and indicators of how scores from each administration were used (e.g., to support a diagnosis, provide feedback to patient). Analysis of variance (ANOVA) will be used to assess for changes in frequency in chart review MBC elements by group (intervention v. comparison site). Provider survey data will be analyzed at the site level as follows. Analysis of the MBC provider surveys will examine differences in attitudes and PROM use by professional group (physicians, nurses, social workers, psychologists, etc.) as well as site. In addition, we will examine change in attitudes over time comparing intervention to comparison sites. As a non-standardized measure, we will be limited to examining frequencies and distributions of responses. Using the TDM, we will calculate ratings for overall team development and the four subfactors of cohesiveness, communication, role clarity, and goals and means. These ratings will be used to assess differences in team development both between and within sites over time. Mean overall clinic/team ORC scores will be calculated as will means on each subscale. Site ORC scores will be considered when interpreting qualitative findings regarding status of MBC implementation. PPAQ-2 data will be analyzed using descriptive statistics and a series of ANOVAs to compare overall site fidelity to the PCMHI model and variations of PPAQ-2 domains across intervention and comparison sites and over time. A descriptive analysis of time data will be conducted, calculating hours spent by the EF and SMEs in support of MBC implementation. We will examine variation in IF time across clinics, types of IF activities, and over time.

Analysis of MBC and QI Team qualitative interview transcripts and facilitation team debriefing notes will be conducted separately using a rapid analysis approach. Text will be coded utilizing qualitative data analysis software, extracted, and summarized for each site to answer target research questions. Site summary results for interviews conducted at two time points will be examined for changes over time.

The application of mixed methods in this design provides the opportunity to advance our understanding of these site changes. Using qualitative data sources, the analysis will yield a more complete description of *how* MBC is implemented in practice at each site. Further, individual site context factors will be incorporated by using ORC, TDM and PPAQ-2 results during qualitative analysis to help explain differences in site implementation status of MBC. For example, it would be expected that sites with low readiness to change (ORC) or low levels of team development (TDM) would be less likely to successfully implement any new practice, including MBC. Conversely, if the EF + QI Team strategy is successful in addressing team development challenges, a given site may experience greater levels of MBC implementation success. Similarly, sites with low PCMHI model fidelity may struggle to keep up with the demands of fast paced primary care clinics and may find the addition of MBC practice is too challenging. Finally, provider attitudes regarding MBC are known to limit uptake [2, 62, 63]. The distribution of clinician attitude and perception responses at sites will be considered when comparing site implementation status of MBC.

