**Methods:**

A mixed-methods, multiple case study design will include 12 PCMHI sites recruited from the 23 PCMHI programs that volunteered to participate in the VA national initiative. Guided by a study partnership panel, sites are clustered into similar groups using administrative metrics. Site pairs are recruited from within these groups. Within pairs, sites are randomized to the implementation facilitation strategy (external facilitation plus QI team) or standard VA national support. The implementation strategy provides an external facilitator and MBC experts who work with intervention sites to form a QI team, develop an implementation plan, and, identify and overcome barriers to implementation. The RE-AIM framework guides the evaluation of the implementation facilitation strategy which will utilize data from administrative, medical record, and primary qualitative and quantitative sources. Guided by the iPARIHS framework and using a mixed methods approach, we will also examine factors associated with implementation success. Finally, we will explore whether implementation of MBC increases primary care team communication and function related to the care of mental health conditions.

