### Implementation facilitation strategy

The implementation facilitation strategy at the six intervention sites will combine expert external facilitation (EF) with an internal QI team to increase the use of MBC for mental health conditions within primary care. A team providing EF at each site will consist of an external facilitator and two to three MBC subject matter experts (SME). The two study external facilitators have expertise in implementation science principles and methods broadly, as well as PCMHI models of care. They each have extensive experience facilitating implementation of evidence-based innovations. Each will lead a facilitation team at intervention sites in supporting QI team members’ efforts to implement MBC.

The facilitation strategy will be applied at each site across three phases, Preparation Phase, Design Phase, and Implementation Phase.

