**Chart reviews**To assess *Effectiveness and Implementation*, data will be extracted from randomly selected subsamples of patient records in the baseline and implementation administrative data pulls for all 12 sites (see Fig. 1). Electronic records of PROM administration and progress notes will be reviewed for each patient encounter during the observation period to extract data for the following variables: patient and provider demographics, dates of encounters, clinic locations, diagnostic codes, mental health PROM use and scores, and text pertaining to assessment and measurement administration/utilization. Progress notes will be reviewed for both the presence and absence of MBC elements, such as evidence that the PROM data played a role in clinical decisions and/or was communicated to the patient or other providers.

**Provider survey: Measurement-based Care Use and Attitudes**Online surveys will be conducted with PCMHI and primary care providers and nurses to capture MBC use (*Effectiveness* and *Maintenance*) at all 12 sites at three time points (see Table 2 and Fig. 1). The survey instrument (Oslin DW, Hoff R, Mignogna J, Resnick SG: Provider attitudes and experience with measurement-based mental health care, submitted), developed for the VA National MBC Initiative and adapted for this study, will assess provider perceptions and attitudes about MBC and frequency of PROM use at key points in care.

**Table 2 Tab2:** Data sources: Factors that may affect MBC implementation

	Facilitation	Context	Innovation	Recipients
Provider survey: MBC Use and Attitudes^a^		X	X	X
Provider survey: TDM^a^		X	X	X
MBC qualitative interviews^a^		X	X	X
Debriefing interviews (IF sites)^a^	X	X	X	X
Time data (IF sites)	X			
QI team interviews (IF sites)^a^	X	X	X	X
Provider survey: ORC		X		
Provider survey: PPAQ-2		X		
Team communication interviews		X		X

*ORC* Organizational Readiness to Change, *TDM* Team Development Measure, *PPAQ-2* Primary Care Behavioral Health Provider Adherence Questionnaire-2

^a^Data sources that also address RE-AIM dimensions evaluating the implementation strategy

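### The ANOVA planned for chart-review elements has no site or pair term although sites were randomised; run on patient records, it can produce too many false positives

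*Protocol article*

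**What the plan says.** The Methods part of the abstract gives the unit of allocation: "Within pairs, sites are randomized to the implementation facilitation strategy (external facilitation plus QI team) or standard VA national support". The same paragraph sets the number of sites ("A mixed-methods, multiple case study design will include 12 PCMHI sites"), and the section on the implementation facilitation strategy puts six of them in the intervention arm.

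Under Effectiveness of EF + QI team strategy, the chart-review paragraph draws its data from "randomly selected subsamples of patient records in the baseline and implementation administrative data pulls for all 12 sites". Each chart is then read encounter by encounter: "Electronic records of PROM administration and progress notes will be reviewed for each patient encounter during the observation period". The data are therefore encounters within patients within sites.

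Aim 1 data analysis describes the charts mainly by descriptive statistics and then names one inferential method: "Analysis of variance (ANOVA) will be used to assess for changes in frequency in chart review MBC elements by group (intervention v. comparison site". The sentence that follows turns to another source: "Provider survey data will be analyzed at the site level as follows". The article gives no number of charts per site, no ICC and no significance level for the chart comparison.

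**The concern.** Records from one site share clinicians, note templates and local policy, so they resemble each other more than records from different sites. When whole sites are randomised, the comparison between arms rests on 12 units however many charts are read. An ANOVA whose only factors are group and period, applied to records, takes its error term from variation among records. If sites drift differently over time for reasons unrelated to facilitation, that error term is too small.

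Charts are the record-based source on whether scores guided treatment and were shared, the second and third elements of measurement-based care. They feed both Effectiveness and Implementation in Table 1. With six sites per arm, unusual change at a few sites could be read as an effect of facilitation.

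**Working it through.** There is no stated figure to reproduce, because the article gives no power, alpha or ICC for the charts. The check asks what a record-level ANOVA would do over a plausible range.

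**Inputs from the article:** 12 sites, 6 v 6; two periods (baseline and implementation); the outcome tested is change by group.

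**Assumptions:** two-sided alpha 0.05; *m* = 10 to 50 charts per site per period; ICC = 0.01 to 0.20; different patients in the two periods; persistence *c*, the share of between-site variance common to both periods, mainly 0.6 to 0.8.

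**Formulas.** With total variance 1, one site's change has variance 2[ICC(1 − *c*) + (1 − ICC)/*m*]. A record-level analysis takes it as about 2/*m*. The ratio is the design effect:

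- change by group: DEFF = 1 + (*m* − 1)·ICC − *m*·ICC·*c*
- one period only: DEFF = 1 + (*m* − 1)·ICC
- true error of the nominal 5% test: 2·[1 − Φ(1.96/√DEFF)]

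**Worked case, *m* = 30, ICC = 0.10.** One period: 1 + 29 × 0.10 = 3.9, error 32%. Change with *c* = 0.8: 3.9 − 30 × 0.10 × 0.8 = 1.5, error 11%. Change with *c* = 0.6: 3.9 − 1.8 = 2.1, error 18%.

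| *m* | ICC | Change, *c* = 0.8: DEFF, error | Change, *c* = 0.6: DEFF, error | One period only: DEFF, error |
|---|---|---|---|---|
| 10 | 0.01 | 1.01, 5.1% | 1.03, 5.3% | 1.09, 6.0% |
| 20 | 0.05 | 1.15, 6.8% | 1.35, 9% | 1.95, 16% |
| 30 | 0.10 | 1.5, 11% | 2.1, 18% | 3.9, 32% |
| 50 | 0.20 | 2.8, 24% | 4.8, 37% | 10.8, 55% |

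The change columns are the relevant ones, because the article plans a test of change. If persistence is only 0.5, the last row gives DEFF 10.8 − 5 = 5.8 and an error of 42%.

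**Simulation.** With 6 v 6 sites, no true effect, a continuous outcome and 20,000 runs per setting (*c* = 0.8 and 0.5), the record-level ANOVA agreed with the formulas within about 1.5 percentage points. A separate simulation with yes/no elements at 30% prevalence (4,000 runs) gave 7–9%, 11–18% and 23–36% for the change contrast in the last three rows.

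**Same simulated data, site as unit.** A t test on the 12 site-level changes (12 − 2 = 10 degrees of freedom) had an error of 4.6% to 5.4% in every setting. A test on the six within-pair differences in change (6 − 1 = 5 degrees of freedom) had 4.7% to 5.3%. Neither a baseline-adjusted comparison nor a mixed model was simulated.

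Treating several encounters of one patient as independent would inflate the error further; this was not modelled.

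**The case against.** The strongest reply is that the article never says the ANOVA is run on records. It speaks of frequencies and names sites in the parenthesis, and an ANOVA on 12 site-level frequencies would fit the same words and be valid. The remark about surveys introduces the surveys and does not define the chart analysis. This stands in part: record level is an inference. It remains the natural one, since the authors specify site level for one source and not for the source just before it.

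A second reply is that a journal article may leave the unit of analysis to a fuller plan. That would hold had the article been silent. Here it names a test and its factor, and the factor alone does not reflect the randomisation.

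Third, a test of change removes stable site differences, and pairing on current use of the measures may reduce imbalance between arms further. The first half is correct and is why the change figures are used. The simulated sites had no pair correlation, so any benefit of pairing is not in the figures. For change, pairing helps only so far as paired sites move together over time.

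Fourth, this is a quasi-experimental multiple case study that draws on several sources together. Chart review is one of four sources for Effectiveness and one of six for Implementation; Reach and Adoption use administrative data. This stands and limits the severity.

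A reader might infer that false positives will certainly be far above 5%, with figures such as 32% or 55%. The documents do not support that. Those figures belong to a comparison of one period, the inputs are assumed, and with few charts and a low ICC the inflation of the change test is negligible.

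**Conclusion.** The point holds as a conditional one. The method named for the chart elements contains nothing that represents the randomised unit. Under its natural reading it can give a false-positive rate for the group-by-period change from about 5% to 37%, that is, from no material inflation to about seven times nominal (37/5 = 7.4).

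That range rests on a two-sided 5% test, 10 to 50 charts per site per period, ICC 0.01 to 0.20, persistence 0.6 to 0.8 and different patients in each period. Lower persistence, or comparing the implementation period alone, raises it. If the authors meant an ANOVA on site-level values, the inflation does not arise and only the wording needs repair.

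Severity is moderate: the chart comparison is one strand among several, but it is a stated inferential test of Aim 1.

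**What to change.** State that the site is the unit of inference for the chart review. For each element, compute one proportion per site and period, and say whether its denominator is reviewed patients or reviewed encounters. Then compare the 12 implementation-period site values between arms, adjusted for each site's baseline value (12 − 3 = 9 degrees of freedom), or analyse the six within-pair differences in change.

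An alternative, which is a different model and not an equivalent one, is a mixed model with random site and site-by-period effects and small-sample degrees of freedom.

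No new data are needed. The cost is a change of wording in Aim 1 data analysis and wider confidence intervals, widest for the pair-level version with its 5 degrees of freedom. The descriptive chart summaries can stay as they are.

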### Site selection and recruitment

A rolling site recruitment approach is used so that four sites will begin study participation every 3 months. Site selection and recruitment processes for each cycle consists of three steps: identification of potential sites, stratification of similar sites into groups, and then recruitment of one or more pairs of sites within those groups. Initially, potential sites are drawn from a pool of 21 VA facilities that self-nominated their PCMHI program to participate in the first phase of the VA National MBC Initiative. In collaboration with the Partnership Panel, we selected administrative data variables (e.g., current use of PROM, site size, staffing and PCMHI program metrics [same-day access and population penetration]), and weighting current PROM use more heavily, we used these variables to stratify sites into relatively similar groups. Prior to each new recruitment cycle, we will draw the same administrative data, excluding participating study sites, to refresh the group placement and the Partnership Panel will review and provide input. If we are unable to recruit 12 sites from within the original pool, we will use the same administrative data variables and collaboration process to identify additional potential sites and group them by similarity. We will continue this process until all 12 sites have been selected and recruited into the study. For each cycle, we will recruit four sites whose PCMHI, primary care and mental health leaders have agreed to participate in study activities. Sites will be randomly assigned to either continued standard national support or the study implementation intervention.

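### The chart-review outcomes are compared by an ANOVA of change by group, although baseline frequencies exist at all 12 sites; this over-corrects chance baseline imbalance and is likely less precise than baseline adjustment unless the site-level correlation is about 0.8 or higher

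*Protocol article*

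**What the plan says.** The Aim 1 data analysis section of the protocol article treats baseline in two ways.

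- **Administrative PROM rates.** The arms are compared "at the end of the intervention and after a sustainment period while controlling for the baseline rate of use".
- **Chart-review elements.** ANOVA "will be used to assess for changes in frequency in chart review MBC elements by group", that is, intervention against comparison sites. No baseline covariate is named and no reason is given for the different treatment.

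The chart reviews paragraph, under Effectiveness of EF + QI team strategy, takes the charts from "randomly selected subsamples of patient records in the baseline and implementation administrative data pulls for all 12 sites". Every site therefore has a baseline frequency for each element. The text reads as two separate samples rather than the same patients followed up, so a baseline covariate would exist at site level.

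On design, the abstract says "A mixed-methods, multiple case study design will include 12 PCMHI sites" and "Within pairs, sites are randomized to the implementation facilitation strategy (external facilitation plus QI team) or standard VA national support". There are six intervention sites, hence six comparison sites. Under Site selection and recruitment, "weighting current PROM use more heavily, we used these variables to stratify sites into relatively similar groups".

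**The concern.** An ANOVA of change scores and a group-by-period ANOVA estimate the same quantity: the difference between arms in mean change. Both subtract the whole of the baseline difference, which fixes the slope of follow-up on baseline at 1. If the true slope is lower, too much is subtracted, and regression to the mean favours the arm that happened to start lower. Baseline adjustment estimates the slope instead.

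This matters for the chart review because it is the record-based source on two of the three elements of measurement-based care: whether scores guided treatment and whether they were shared. The administrative comparison covers administration and entry of the measures. Surveys and interviews add self-report. With six sites per arm, chance imbalance in these elements can be large. Matching leans on current PROM use, which may balance use and sharing of scores only in part.

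**Working it through.** The plan states no power, alpha, SD, number of charts or correlation, so there is no figure of its own to reproduce.

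**Inputs.** From the article: 12 sites, six per arm, randomised within pairs. Assumed: site-level SD of 1 in both periods, correlation rho (range shown), true effect 1.4 SD, two-sided 5%. For the matched case, both sites of a pair share a proxy that correlates 0.7 with the baseline frequency.

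**1. Over-correction.** Given a baseline arm difference D, the change contrast is shifted by (rho − 1) × D. Simulated slopes agree: −0.70 at rho 0.3, −0.51 at 0.5, −0.30 at 0.7, −0.10 at 0.9. The typical size of D is its standard error:

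- unmatched: sqrt(2/6) = 0.58 SD
- matched: sqrt((2/6) × (1 − 0.7²)) = sqrt(0.333 × 0.51) = 0.41 SD

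At rho 0.5 the typical over-correction is 0.5 × 0.58 = 0.29 SD unmatched and 0.5 × 0.41 = 0.21 SD matched.

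**2. Variance with 12 sites, unmatched.** Relative to a comparison of follow-up alone, change has variance 2(1 − rho). Baseline adjustment has (1 − rho²) × (1 + 1/8), where the 1/8 is the cost of estimating a slope from 12 sites. The ratio of change to adjusted is 2/[(1 + rho) × 1.125].

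- rho 0.5: 2/(1.5 × 1.125) = 1.19
- rho 0.7: 2/(1.7 × 1.125) = 1.05
- rho 0.9: 2/(1.9 × 1.125) = 0.94
- break-even: 1 + rho = 2/1.125, so rho = 0.78

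Simulation gives 1.37 at rho 0.3, 1.19 at 0.5, 1.05 at 0.7 and 0.94 at 0.9. Under the matched scenario the simulated ratio at rho 0.5 is 1.10. Change variance at rho 0.5 is thus about 10% to 19% higher.

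**3. Power, by simulation.** Change is tested on 10 degrees of freedom and baseline-adjusted on 9, both at site level without pair terms, with sites matched as above:

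| rho | change | adjusted |
|---|---|---|
| 0.3 | 46% | 60% |
| 0.5 | 60% | 68% |
| 0.7 | 81% | 83% |
| 0.8 | 94% | 93% |

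Without matching at rho 0.5, the figures are 59% and 66%. Type I error of the adjusted test was 0.05 with and without matching. The unpaired change test ran conservative under matching (about 0.03 to 0.05), which is part of its disadvantage in the table.

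**4. Is a low rho plausible?** Separate chart samples add sampling error to both site frequencies. With v the between-site variance and s = p(1 − p)/m for m charts per site and period, observed rho = true rho × v/(v + s). Assume p = 0.30 and a between-site SD of 0.10, so v = 0.01 and s = 0.21/m. A true rho of 0.7 to 0.9 then becomes:

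- m = 10: 0.23 to 0.29
- m = 20: 0.34 to 0.44
- m = 50: 0.49 to 0.63

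These values lie below the break-even, but they rest on assumed inputs.

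**The case against.** **The article is condensed.** It gives this comparison one sentence, and covariates are often left to a fuller document. That would excuse silence. Here the estimand is stated, a change in frequency by group, beside a sentence in the same section that does adjust for baseline. The quantity named is what over-corrects, whatever detail follows.

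**Change is a legitimate comparison.** It is unbiased on average under randomisation, and two data sources may be analysed differently. This stands. A reader might infer that the planned analysis is biased or that the section contradicts itself. It does not support either: the over-correction is conditional on the imbalance that happens to occur.

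**Few sites weaken the case.** Estimating a slope from 12 points costs precision, so large-sample gains overstate the benefit. This stands. A reader might infer that precision is certainly lost because there are only 12 sites. The documents do not support that: they give no rho, the loss disappears near 0.8, and at 0.9 adjustment is slightly worse.

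**The pairs are ignored.** If both methods are run on six pair differences in the matched scenario, change beats adjusted: 44% v 42% at rho 0.3, 55% v 48% at 0.5, 74% v 64% at 0.7 and 88% v 77% at 0.8. This limits how the adjustment should be done, but does not defeat it. The adjusted analysis on 12 sites still beats the paired change test at every rho tried, for example 68% v 55% at 0.5 and 93% v 88% at 0.8.

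**Matching and purpose.** Grouping on PROM use may also balance use and sharing of scores to an unknown degree, so it would be too strong to say that these elements are left uncontrolled. The study is a mixed-methods case study that triangulates sources, and power is not its stated basis. Both points reduce the weight of the concern, but the arm comparison is still planned.

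**Conclusion.** The concern holds in a conditional form. The stated change comparison over-corrects chance baseline imbalance for any rho below 1, typically by 0.21 to 0.29 SD at rho 0.5. It is likely less precise than baseline adjustment unless rho is about 0.8 or higher. The power difference is about 14 points at rho 0.3, 8 at 0.5 and 2 at 0.7, and about 1 point the other way at 0.8. Rho, the 1.4 SD effect and the strength of matching are assumptions. The direction at low to moderate rho is firm; the size in this study is not known. The change is worth making because the baseline data are already planned and the possible loss is small.

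**What to change.** Replace the ANOVA sentence for the chart-review elements with wording such as:

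> For each chart-review MBC element, the site's implementation-period frequency will be regressed on study arm, with the site's baseline-period chart-review frequency as covariate (12 sites), as for the administrative rates. The adjusted arm difference will be reported with its 95% confidence interval. Raw change per site will be shown descriptively.

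The plan should also say that the model is fitted to the 12 sites, because adjusting within six pair differences costs more precision.

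The cost is one sentence and one residual degree of freedom (9 instead of 10), with no new data. At a rho of 0.8 about 1 point of power is lost. That figure is for the site-level model without pair terms.
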